In this study, the primary outcome is the change in FEV_1_, with a significance level (α) set at 0.05 and a test power (1-β) set at 0.8. The number of participants was determined using g-power, considering a two-sided test and an allocation ratio of 1:1 [11]. As a result, the effect size was calculated to be 0.437, and the total number of participants was 168. Taking into account the number of recruitable participants, the minimum scope for validity assessment, and a dropout rate of 15%, the total number of participants was determined to be 198 to secure the minimum necessary sample size.

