### Outcome measurements

#### Primary outcome

##### Pulmonary function test (Forced Expiratory Volume in 1 s, FEV_1_)

Spirometry is a test that plays an essential role in the diagnosis and monitoring of asthma to identify airflow limitation [2]. Using spirometry, measurements of forced vital capacity (FVC), FEV_1_, among others are taken, and changes in FEV_1_% and liters are observed to measure the amount of change. The primary outcome of this study will be the average change in FEV_1_ scores between baseline and week 8.

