### Statistical analysis

#### Effectiveness outcomes

Statistical analyses are conducted independently by a statistical expert using SAS. In the two-tailed tests, the level of significance is set at 0.05. All analyses primarily utilize intention-to-treat analysis, with per-protocol analysis conducted concurrently, and the results are presented together. In the demographic baseline data, continuous variables are presented as mean and standard deviation and are analyzed using an independent t-test or Mann–Whitney U test. Categorical variables are presented as frequency and proportion and analyzed using a chi-square test or Fisher's exact test (when the expected frequency is less than 5 in more than 25% of all values).

The primary efficacy evaluation is based on the mean change in FEV_1_ scores evaluated at week 8 (56 days post-dosing), whereas secondary efficacy evaluations compare the means of PEF, FVC, FEF25–75, FeNO, ACT scores, AQLQ scores, Serum IgE, eosinophil count, CRP, and the frequency of rescue medication use assessed at baseline and weeks 4 and 8. If the assumption of normality is satisfied, an independent t-test is conducted; otherwise, the Mann–Whitney U test is applied. However, if significant differences between the groups are found in baseline values, an analysis of covariance (ANCOVA) is performed. Missing data is replaced using the last observation carried forward method; each missing value is replaced with the participant's last observed value. For the secondary efficacy evaluation, the distribution of participants according to each diagnosis of Korean medicine pattern identification assessed at baseline is presented as frequency and proportion and visualized in tables or graphs through descriptive analysis.

Subgroup analysis will be performed according to the following criteria: First, subgroups will be divided according to the type of asthma medication (ICS or ICS + LABA) taken in addition to the LTRA at enrollment. Second, the effect will be further analyzed by age, separating younger patients (< 35 years) from older patients (> 60 years). Third, subgroups will be defined as male and female. Fourth, subgroups will be created based on severity as measured by ACT, ≤ 15 and > 15. Finally, subgroup analyses will be performed according to Korean medicine pattern identification.

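### The primary FEV1 test depends on a normality check and a baseline significance test; one baseline-adjusted ANCOVA in litres should be named in advance

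*Protocol article*

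**What the plan says.** The primary outcome section of the protocol article declares a mean: "The primary outcome of this study will be the average change in FEV_1_ scores between baseline and week 8". Its preceding sentence has spirometry followed as per cent and litres ("and liters are observed to measure the amount of change") and does not say which scale is primary.

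The Effectiveness outcomes section then gives the test: "If the assumption of normality is satisfied, an independent t-test is conducted; otherwise, the Mann–Whitney U test is applied". The next sentence overrides this: "However, if significant differences between the groups are found in baseline values, an analysis of covariance (ANCOVA) is performed". It does not say which baseline values count. The rule covers the primary and the secondary efficacy outcomes. The Safety analysis section repeats it for the laboratory values, and there it does name the variables.

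The Sample size section is built on an unadjusted two-sample comparison of change in litres, with "significance level (α) set at 0.05 and a test power (1-β) set at 0.8" and "considering a two-sided test and an allocation ratio of 1:1". Its result is that "the effect size was calculated to be 0.437, and the total number of participants was 168".

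**The concern.** The one confirmatory comparison has three possible forms, and the data decide between them.

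- **The target moves.** A t-test on change estimates a difference in mean change, ANCOVA estimates an adjusted mean difference, and Mann–Whitney is a rank comparison that does not test the declared mean change.
- **The trigger answers the wrong question.** Allocation is random, so any baseline difference is chance. Whether adjustment helps depends on how strongly baseline FEV1 predicts week-8 FEV1, and a baseline p-value says nothing about that.
- **The default uses baseline inflexibly.** A change score subtracts baseline with slope 1. If the true regression slope differs from 1, imbalance is mis-corrected and some precision is lost. An imbalance just short of significance leaves that default in place.
- **The branches fit together poorly.** Non-normal data go to a rank test unless baseline also differs, in which case they go to a normal-theory model.

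At stake are a prespecified primary estimate, some power, and protection against bias in trials with a near-significant imbalance.

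**Working it through.** **Inputs.** From Table 2 of the Sample size section: test group SD 0.30 before and 0.75 after; control group SD 0.25 before and 0.80 after; mean changes 1.72 − 0.88 = 0.84 and 1.37 − 0.89 = 0.48, a difference of 0.36 L. (The text prints 0.39 for the control change, but the stated effect size follows from 0.48.) The plan assumes a pre–post correlation of r = 0. Other values of r below are assumptions.

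**1. Reproduce the plan.** Change SDs at r = 0 are √(0.30² + 0.75²) = 0.808 and √(0.25² + 0.80²) = 0.838, pooled 0.823. Effect size: 0.36 / 0.823 = 0.437. Noncentral t, two-sided 0.05, gives 84 per arm (power 0.804), so 168 in total; 168 / 0.85 = 197.6, so 198. The plan's figures reproduce.

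**2. Change score against ANCOVA.** Pooled SDs: before √((0.30² + 0.25²)/2) = 0.276; after √((0.75² + 0.80²)/2) = 0.775.
- Change SD = √(0.276² + 0.775² − 2·r·0.276·0.775)
- ANCOVA residual SD = 0.775·√(1 − r²)
- True baseline slope = r·0.775/0.276, which equals 1 at r = 0.276/0.775 = 0.36

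Power for 0.36 L at 84 per arm:

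| r | slope | change SD | ANCOVA SD | power, change | power, ANCOVA |
|---|---|---|---|---|---|
| 0 (plan) | 0 | 0.823 | 0.775 | 0.805 | 0.849 |
| 0.36 | 1.0 | 0.725 | 0.725 | 0.893 | 0.893 |
| 0.5 | 1.4 | 0.681 | 0.672 | 0.926 | 0.932 |
| 0.7 | 2.0 | 0.615 | 0.554 | 0.965 | 0.987 |

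At r = 0 the variance ratio is 0.775²/0.823² = 0.887. By the normal approximation that is 73 per arm for ANCOVA against 83 for change.

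**3. How often the trigger fires.** Taking it as baseline FEV1 tested at two-sided 0.05, randomisation alone makes it fire in about 5% of trials. In 20,000 simulated trials per setting (normal data, 84 per arm) the rate was about 5% throughout. Power of the conditional rule against ANCOVA always: 0.81 against 0.85 at r = 0, and 0.968 against 0.987 at r = 0.7.

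**4. Near-miss imbalance.** The standard error of the baseline difference is 0.276·√(2/84) = 0.0426 L, so an imbalance just short of p = 0.05 is 1.96 × 0.0426 = 0.084 L. The change-score difference is shifted by (slope − 1) × imbalance. At r = 0 that is the full 0.084 L in size, and 0.084/0.36 = 23% of the planned effect. At slope 1 it is zero. More typically, in simulated trials with baseline p between 0.05 and 0.20, the mean shift was about 0.06 L at r = 0. The null rejection rate in those trials was 0.067 for the change score and 0.048 for ANCOVA.

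**5. Overall type I error.** For the conditional rule across all trials it was 0.032 to 0.049 in the simulated settings, so not inflated. The normality branch was not simulated.

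**The case against.** The best defence is that this is a stated rule, not a free choice. The data analysts are blinded, and the baseline trigger looks at baseline values rather than outcome. The trial is sized for exactly the default test, so no promised power is lost: 80% holds at r = 0 and rises with r. Averaged over randomisation, the change-score comparison is unbiased. All of this stands, and it limits the size of the point.

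It also rules out several stronger readings:

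- **False positives.** A reader might infer that choosing the test from the data inflates type I error. The check of the baseline trigger shows that it does not.
- **Baseline ignored.** A reader might infer that imbalance goes uncorrected. A change score does correct it, with a fixed slope that may be wrong.
- **Large power loss.** Assuming equal SDs before and after, at r = 0.5, one can obtain about 82% against 90%. That needs both SDs at 0.823 L, a baseline SD three times the plan's 0.276. At the plan's SDs the gap at r = 0.5 is 0.6 points.
- **Six analyses.** Multiplying three tests by two scales overstates the matter. The sentence on per cent and litres describes measurement, and the sizing is wholly in litres. The scale is a separate, smaller ambiguity.

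What the defence does not supply is a reason for the trigger. The baseline p-value remains uninformative about the need to adjust, and the rank branch still departs from the declared mean change. An unseen analysis plan does not cure this, because the article states the rule affirmatively.

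**Conclusion.** The point holds at moderate size. The primary test and its estimand are not fixed in advance, and the condition for baseline adjustment has no statistical basis in a randomised trial. At the plan's own inputs the avoidable loss is about 4 power points at r = 0, nil near r = 0.36, and about 0.6 and 2 points at r = 0.5 and 0.7. ANCOVA is not materially worse at any r. The 0.08 L shift is an extreme case, needing an imbalance at the edge of significance together with r = 0.

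These figures rest on the Table 2 SDs, roughly normal data, 84 evaluable per arm, and baseline FEV1 as the triggering variable. The plan's r = 0 is itself a placeholder chosen for want of references, so the power gain in this trial could lie anywhere in the range shown.

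**What to change.** In the Effectiveness outcomes section, name one primary analysis: ANCOVA of week-8 FEV1 in litres, the scale of the sample-size calculation, on treatment and baseline FEV1. Report the adjusted mean difference with its 95% confidence interval whatever the baseline or normality tests show. Delete the baseline-significance trigger there, and the same trigger in the Safety analysis section. Keep Mann–Whitney as a sensitivity analysis and make FEV1 per cent secondary.

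The change costs protocol and analysis-plan wording only. Baseline FEV1 is already collected, and 168 evaluable participants (198 randomised) remain sufficient on the plan's own assumptions. The amendment should be made before the data are unblinded.

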### Concomitant medications

During the clinical trial participation period, the participant is advised not to take any medications other than the investigational product. However, if another medication is administered in combination at the investigator’s discretion, information regarding the medication (such as name, daily dose, administration period, and reason for administration) must be recorded in the case report form (CRF). Drug history is checked for all preceding/concurrent medications within four weeks based on the screening point.

The use of new medications that influence the results of a clinical trial during the administration period of an investigational product is prohibited. The use of emergency medications is not prohibited if a patient's asthma-related symptoms worsen temporarily. However, if a patient's asthma symptoms persistently worsen and additional medications such as systemic oral steroids, theophylline, other xanthine drugs, anti-IgE antibodies, and persistent anticholinergic bronchodilators are needed for continuous control, the clinical trial is halted and the relevant medication is administered. This is not applicable in cases where they are used momentarily for the short-term treatment of acute exacerbation of asthma.

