### Safety analysis

All adverse reactions that have occurred are presented by severity and causal relationship with the test drug, and the incidence rates of adverse reactions, adverse reactions that caused dropout, and serious adverse reactions are analyzed. For clinical trial subjects who dropped out due to treatment failure or adverse reactions, the proportion of each group is presented along with a 95% confidence interval. Chi-square analysis or Fisher's exact test is performed on the observed and expected frequencies.

The mean differences in AST, ALT, ALP, TB, GGT, BUN, creatinine, and eGFR levels at baseline, week 4, and week 8 are compared. If the assumption of normality is satisfied, an independent t-test is performed, and if the assumption of normality is not met, a Mann–Whitney U test is conducted. However, if a significant difference between the groups is found in the baseline values of AST, ALT, ALP, TB, GGT, BUN, creatinine, and eGFR, an ANCOVA is performed. The missing values are estimated and replaced using the stochastic regression imputation method.

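### LOCF is the only stated method for missing week-8 FEV1 although withdrawal depends on outcome, so the primary comparison can be biased in either direction

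*Protocol article*

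**What the plan says.** The primary outcome is defined in the Primary outcome section: "The primary outcome of this study will be the average change in FEV_1_ scores between baseline and week 8". The analysis set is given under Effectiveness outcomes: "All analyses primarily utilize intention-to-treat analysis, with per-protocol analysis conducted concurrently". The same section fixes how gaps are filled: "Missing data is replaced using the last observation carried forward method". The article states no other method for missing efficacy data.

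Several passages tie leaving the trial to how the patient is doing. Under Concomitant medications, if symptoms persistently worsen and further continuous medication is needed, "the clinical trial is halted and the relevant medication is administered". The Withdrawal criteria add adverse reactions, additional drugs that could affect asthma treatment, a changed LTRA prescription and compliance below 70%; Drug interventions repeats the compliance rule. The Safety analysis section foresees dropout for treatment failure and for adverse reactions.

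The Sample size section sets the design "with a significance level (α) set at 0.05 and a test power (1-β) set at 0.8" and reports that "the effect size was calculated to be 0.437, and the total number of participants was 168". It then raises 168 to 198 for 15% dropout.

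For laboratory safety values the plan uses a different single imputation: "The missing values are estimated and replaced using the stochastic regression imputation method".

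**The concern.** LOCF assumes that a patient's FEV1 stays at its last measured value until week 8. The withdrawal rules make that hard to believe. Unless spirometry is repeated at exit, a patient who leaves because of worsening enters the week-8 comparison with a value from before the worsening. A patient lost before any post-baseline spirometry is scored as exactly zero change. The t-test or ANCOVA then treats these values as measurements.

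If dropout rates or reasons differ by arm, part of the estimated difference reflects who left and when, not what the treatment did. The concurrent per-protocol analysis does not test the assumption, because it would normally leave out the patients in question.

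There is also a mismatch with the sample size. The 15% inflation treats dropouts as lost and leaves 168 analysed, whereas the planned analysis keeps all 198 with some values carried. The stated power therefore does not describe the planned analysis.

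**Working it through.** **1. Reproducing the plan's figures.** Inputs are from Table 2, with the pre-post correlation of zero that the plan assumes.

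- SD of change, test: √(0.30² + 0.75²) = √0.6525 = 0.808. Control: √(0.25² + 0.80²) = √0.7025 = 0.838. Pooled: √0.6775 = 0.823.
- Mean change, test: 1.72 − 0.88 = 0.84 L. Control: 1.37 − 0.89 = 0.48 L. The text under Table 2 gives 0.39 for control, but only 0.48 yields the stated effect size, so 0.48 is used here.
- d = (0.84 − 0.48)/0.823 = 0.437. A two-sided t-test at 0.05 needs 84 per arm (168), with power 80.4%. 168/0.85 = 197.6, hence 198. If all 198 were observed, power would be 86.5%.

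**2. Power under LOCF with 99 per arm and 15% dropout in both arms.** Where patients are lost is not stated, so three cases are shown. Let a be the share carried from baseline (change 0) and b the share carried from week 4. Assume the week-4 value holds half the mean change, with an SD of r times the week-8 SD, r from 0.75 to 1. Then for each arm:

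- mean = (1 − a − b)μ + 0.5bμ
- variance = (1 − a − b)(s² + μ²) + b(r²s² + 0.25μ²) − mean²

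All carried from baseline (a = 0.15, b = 0):

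- Means: 0.85 × 0.84 = 0.714 and 0.85 × 0.48 = 0.408; difference 0.306 L.
- Variances: 0.85(0.6525 + 0.7056) − 0.714² = 0.6446 and 0.85(0.7025 + 0.2304) − 0.408² = 0.6265; pooled SD 0.797.
- d = 0.384.

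| Pattern of the 15% | Difference (L) | Power |
|---|---|---|
| All from baseline | 0.306 | 76.6% |
| Half baseline, half week 4 | 0.3195 | 78.3% to 79.7% |
| All from week 4 | 0.333 | 80.0% to 82.5% |

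In the first row the SD falls from 0.823 to 0.797 only because constants have been inserted as data. With baseline carried and equal dropout at other rates, power is 80.2% at 10% and 72.8% at 20%.

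**3. Unequal dropout with the planned effect, baseline carried.** 20% test and 10% control: difference 0.240 L, power 55.3%. 10% test and 20% control: difference 0.372 L, power 90.9%. The true effect is 0.36 L in both cases.

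**4. Unequal dropout with no drug effect.** Assume both arms gain 0.48 L, half of it by week 4, with dropout split evenly before and after week 4.

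- 10% test: 0.90 × 0.48 + 0.05 × 0.24 = 0.444. 20% control: 0.80 × 0.48 + 0.10 × 0.24 = 0.408. Spurious difference 0.036 L; type I error about 6.1% to 6.2%.
- 5% test versus 25% control: 0.462 − 0.390 = 0.072 L; type I error about 9.6%.
- If both arms gain only 0.10 L, the 10% versus 20% case gives 0.0075 L and about 5.1%.

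Swapping the arms reverses the sign. At equal rates the spurious difference is zero.

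**5. Withdrawal for worsening.** Step 4 lets leavers miss a gain. Suppose instead that their true week-8 change is x litres below the carried value. LOCF then shifts the treatment difference by x × (test rate − control rate). For x = 0.3 L and rates of 20% and 10% this is 0.3 × 0.10 = 0.03 L in favour of whichever arm loses more patients. That is opposite in direction to step 4.

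**The case against.** Much of the opposing case stands.

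- **Power.** A reader might infer that LOCF necessarily takes power below 80%. The documents do not support that. The 76.6% requires every dropout to be carried from baseline; once some have a week-4 value, the loss is under 2 points or nil. The inflation to 198 is ordinary practice, correctly computed, and largely offsets the dilution.
- **Size of bias.** The dropout split, its timing and the share of gain at week 4 are assumptions. The 0.48 L comes from the control arm of the cited Bufei granule study, and nothing shows that placebo patients already on treatment here would gain as much. The bias falls in proportion to the gain. With equal dropout and equal reasons, LOCF shrinks a real effect and does not invent one.
- **Spirometry at exit.** The article does not say whether FEV1 is measured at withdrawal; Table 1 and the full protocol are not shown. Short-term exacerbation treatment is also exempt from the halting rule, so not all worsening leads to missing data.
- **MMRM.** It assumes missing at random. If worsening after the last visit causes withdrawal, an MMRM can be more favourable than LOCF, so it is not a cure by itself.
- **Laboratory values.** A reader might infer that imputing them masks harm. That goes too far. Adverse reactions, including those causing dropout, are tabulated separately with dropout proportions per arm, and clinically significant changes found through blood tests are recorded as adverse events.

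None of this makes LOCF credible here. It is a stated primary method, not a detail left to an analysis plan, and its assumption conflicts with the protocol's own withdrawal rules.

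**Conclusion.** The point holds as a fault in the stated primary method. Filling week-8 FEV1 by LOCF, when withdrawal depends on worsening, adverse reactions and compliance, can bias the comparison in either direction if dropout differs by arm. Neither the size nor the sign can be fixed from the documents, which give only an overall 15%. Under the assumptions of step 4, a 10% versus 20% imbalance gives 0.036 L, a tenth of the planned 0.36 L, with type I error about 6%. Both are smaller with a smaller gain.

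Power is a lesser matter: about 77% to 83% at 15% dropout in both arms. A material loss needs more dropout than planned or an excess in the test arm.

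The single stochastic regression imputation of laboratory values is a secondary, minor weakness. It puts model predictions in place of results from people who left, but it does not remove the separate reporting of harms.

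**What to change.** - Replace LOCF as the primary method. Use an MMRM of change in FEV1 at weeks 4 and 8 with baseline FEV1, treatment, visit and treatment-by-visit, and read the treatment difference at week 8. Multiple imputation is an acceptable alternative.
- State in the Primary outcome section that week-4 FEV1 is used. That section names only baseline and week 8, although spirometry for the secondary outcomes is scheduled at week 4 and the Economic evaluation section lists effectiveness measurements at all three visits.
- Add a delta-adjusted or reference-based sensitivity analysis, since withdrawal for worsening may be missing not at random.
- As a minor change, analyse the laboratory safety values as observed and drop the stochastic regression imputation.

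The cost is revised wording in the analysis section, modest programming and possibly slightly wider confidence intervals. It calls for no extra patients and, if FEV1 is recorded with the week-4 spirometry, no extra visits. The change should be made before unblinding.

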### Sample size

The current study requires a total of 168 test subjects. Considering a dropout rate of 15%, the sample size will be adjusted to 198.

The required number of recruits per group was calculated with reference to the study conducted in 2019 [10]. According to the reference literature, the changes in forced expiratory volume in the first second (FEV_1_) after 8 weeks of Bufei granule administration in a total of 178 subjects, with 89 in the test group and 89 in the control group, are as follows (Table 2).

**Table 2 Tab2:** Changes in FEV_1_ (L) observed in the study by Xin X and Peng F (2019) [10]

	FEV_1_ (L) before treatment	FEV_1_ (L) after treatment
Test group (*n* = 89)	0.88 ± 0.30	1.72 ± 0.75
Control group (*n* = 89)	0.89 ± 0.25	1.37 ± 0.80

As the primary outcome of this study is the variation in FEV_1_, the calculation of FEV_1_ changes was based on the aforementioned study. The mean change in FEV_1_ in each group was calculated as the difference between the post-treatment and pre-treatment means. The standard deviation was calculated based on the following formula, considering the pre-treatment standard deviation, post-treatment standard deviation, and the correlation between measurements taken pre- and post-treatment:$$\mathrm{Mean}\;\mathrm{change}\;\mathrm{in}\;{\mathrm{FEV}}_1\;=\;\mathrm{Post}-\;\mathrm{treatment}\;\mathrm{mean}\;\;-\;\;\mathrm{Pre}-\mathrm{treatment}\;\mathrm{mean}$$$$\mathrm{Standard}\;\mathrm{deviation}\;\mathrm{of}\;{\mathrm{FEV}}_1\;\mathrm{change}\;=\;{({\mathrm{Pre}-\mathrm{treatment}\;\mathrm{standard}\;\mathrm{deviation}}^2\;+\;{\mathrm{Post}-\mathrm{treatment}\;\mathrm{standard}\;\mathrm{deviation}}^2\;-\;2\;\ast\;\mathrm{Correlation}\;\mathrm{coefficient}\;\mathrm{between}\;\mathrm{pre}-\;\mathrm{and}\;\mathrm{post}-\mathrm{treatment}\;\mathrm{measurements}\;\ast\;\mathrm{pre}-\mathrm{treatment}\;\mathrm{standard}\;\mathrm{deviation}\;\ast\;\mathrm{post}-\mathrm{treatment}\;\mathrm{standard}\;\mathrm{deviation})}^{(1/2)}$$

The correlation coefficient between the pre- and post-treatment measurements was conservatively assumed to be zero because of a lack of related references. The calculated FEV_1_ change from this reference paper was found to be 0.39 ± 0.838 for the control group and 0.84 ± 0.808 for the test group.

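### The age subgroup is defined only as under 35 and over 60, so participants aged 35 to 60 belong to neither stratum and this analysis omits them without a stated reason

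*Protocol article*

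**What the plan says.** The subgroup paragraph of the protocol article (Statistical analysis, Effectiveness outcomes) lists five factors: background asthma drug, age, sex, asthma control by ACT score, and Korean medicine pattern.

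- Age is handled by "separating younger patients (< 35 years) from older patients (> 60 years"). No third band is named.
- Sex and asthma control are split without a gap: "subgroups will be defined as male and female" and "subgroups will be created based on severity as measured by ACT, ≤ 15 and > 15".
- Background drug is ICS or ICS plus LABA, which matches the two regimens admitted by the inclusion criteria.
- For the last factor, "subgroup analyses will be performed according to Korean medicine pattern identification".

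The inclusion criteria admit adults aged 19 to 85. Nowhere does the article assign ages 35 to 60 to an age subgroup, or say that a comparison of the extremes is intended. The Sample size section plans 168 evaluable and 198 recruited participants and does not refer to subgroups.

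**The concern.** A subgroup factor should place every randomised participant somewhere, or the plan should say why it does not. Here the two cut-offs leave the middle of the eligible age range unassigned. Both inequalities are strict, so a participant aged exactly 35 or exactly 60 is also outside. The drug, sex and ACT splits in the same paragraph have no such hole, which suggests an oversight, though the article does not settle that.

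At stake is what the trial can say about age. Any statement about how the effect of CSBHT varies with age would rest on the two ends of the range and give no estimate for patients between 35 and 60. Closing the gap after the data are unblinded would also look data-driven, because the new cut-offs would be chosen with the results in view.

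This is not detail left to a separate analysis plan. The article states the cut-offs, and as stated they do not cover the trial population.

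**Working it through.** **1. The plan's own figure.** The article gives no figure for the age subgroups, so the only one to reproduce is the total sample size.

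- Inputs, from Table 2: pre- and post-treatment SDs 0.25 and 0.80 (control), 0.30 and 0.75 (test); mean changes 1.37 − 0.89 = 0.48 and 1.72 − 0.88 = 0.84; pre-post correlation taken as zero.
- SD of change: √(0.25² + 0.80²) = 0.838 and √(0.30² + 0.75²) = 0.808. Pooled: √((0.838² + 0.808²)/2) = 0.823.
- Effect size: (0.84 − 0.48)/0.823 = 0.437.
- The design is stated "with a significance level (α) set at 0.05 and a test power (1-β) set at 0.8", "considering a two-sided test and an allocation ratio of 1:1". A two-sample t-test then needs 83.17 per arm, rounded up to 84, or 168 in total.
- Dropout: 168/(1 − 0.15) = 197.6, rounded up to 198.

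This agrees with "the effect size was calculated to be 0.437, and the total number of participants was 168" and "Considering a dropout rate of 15%, the sample size will be adjusted to 198". The age gap does not enter this calculation. (The text prints the control change as 0.39, whereas Table 2 gives 0.48. Only 0.48 yields 0.437. That is a separate matter and does not bear on this point.)

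**2. Width of the gap.** Counting whole years of age:

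- eligible: 85 − 19 + 1 = 67
- under 35 (19 to 34): 34 − 19 + 1 = 16
- over 60 (61 to 85): 85 − 61 + 1 = 25
- neither (35 to 60): 60 − 35 + 1 = 26

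Check: 16 + 26 + 25 = 67. Share in neither stratum: 26/67 = 38.8%.

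**3. Participants affected.** The article gives no age distribution, so the share aged 35 to 60 is an assumption. Number left out = share × 198.

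| Assumed share aged 35–60 | Left out of 198 | In a stratum |
|---|---|---|
| 20% | 40 | 158 |
| 30% | 59 | 139 |
| 38.8% (uniform ages) | 77 | 121 |
| 50% | 99 | 99 |
| 60% | 119 | 79 |

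Under uniform ages the 121 split into about 47 under 35 (198 × 16/67) and 74 over 60 (198 × 25/67).

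**4. Is the loss one of precision or of coverage?** Take uniform ages and 80% power at two-sided 0.05 (multiplier 2.80).

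- As written, the detectable treatment-by-age difference is 2.80 × √(4/47 + 4/74) = 1.04 SD.
- An even two-way split of all 198 gives 2.80 × √(4/99 + 4/99) = 0.80 SD.

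These two figures are not like for like, because the extreme strata lie further apart in age. Their mean ages are 26.5 and 73, a distance of 46.5 years. An even split at 52 gives mean ages of about 35.5 and 68.5, a distance of 33 years.

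Per year of age, if the effect changes linearly:

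- as written: 1.04/46.5 = 0.022 SD
- even split: 0.80/33 = 0.024 SD
- continuous age in all 198: 2.80 × 2/√(198 × 374) = 0.021 SD, where the variance of age is (67² − 1)/12 = 374

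For a straight-line trend the stated strata therefore lose little precision. What they lose is coverage: no estimate for ages 35 to 60, and no means of seeing whether a straight line is adequate.

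**The case against.** The best defence has four parts.

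**Only one analysis is touched.** This stands in full. Age is one of five subgroup factors. Participants aged 35 to 60 remain in the intention-to-treat comparison and in the drug, sex, ACT and pattern analyses. A reader might infer that these people are discarded from the trial's results, but nothing in the article supports that.

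**A contrast of extremes is a legitimate choice.** This stands in part. Step 4 shows that it is reasonably efficient for a linear trend, so a claim that most of the information on age is thrown away would be wrong. But the article does not say that such a contrast is intended, and the contrast still leaves the middle undescribed.

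**The size is unknown.** This stands. A reader might infer that the age question is answered on a minority of patients, or on very few young ones. The article has no age distribution to support either. Under uniform ages, 121 of 198 (61%) remain and about 47 are under 35.

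**Subgroup testing is not specified here.** This also stands. A reader might count subgroup cells and compute a chance of at least one false positive. The subgroup paragraph names factors and cut-offs but no subgroup test and no within-cell p-values, and such detail is commonly left to the analysis plan. The number of cells is open too. The article describes a deficiency/excess division, seven patterns and a separate cold-heat questionnaire, without saying which defines the subgroups. The factors also re-cut the same participants, so a calculation that treats the cells as independent would not apply.

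None of this closes the gap in the age bands.

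**Conclusion.** The point holds in a narrow form. The stated age strata omit ages 35 to 60 inclusive, which is 26 of 67 eligible years (39%), and no reason is given. That much follows from the two cut-offs and the inclusion criteria alone.

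The head count rests on an assumption. A share of 20% to 60% gives about 40 to 119 of 198 outside both strata, and uniform ages give 77. The omission does not affect the primary analysis, the other subgroups or the sample size. It is no ground for saying that the age analysis uses only a minority of participants, or for alleging inflated false-positive rates across subgroups. It is a small defect in a stated rule, worth correcting because the correction uses data already collected.

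**What to change.** Before unblinding, reword the age item so that every participant contributes. Either of these would do:

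- three exhaustive bands (under 35, 35 to 60 inclusive, over 60), which also places ages exactly 35 and exactly 60; or
- age as a continuous variable in a treatment-by-age interaction.

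Report the estimate with its 95% confidence interval and label it exploratory. If the contrast between the youngest and oldest patients is of particular interest, it can be shown alongside, with the reason stated.

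The cost is analysis wording only, with no extra data, visits or participants. The downside is negligible: one more band to report, or one model term.
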